**Figure 2 F2:**
[figure not shown]
**Conformation of the cluster per country.** PHCs: Primary Health Centers.

In Argentina, we have selected 10 clusters composed of the maternity hospitals and the associated prenatal clinics at health centers. Each hospital has two or three associated prenatal clinics, located in primary health centers in the surrounding area (where women attend prenatal care until 34–36 weeks of pregnancy). In Uruguay, we have selected 10 prenatal clinics; each clinic forms one cluster. All women receiving antenatal care at the participating prenatal clinics will be eligible to receive the “5 A’s” intervention.

### Randomization procedures

The conformation of the cluster will be different in each country. Thus, we will consider the following as a cluster: groups of prenatal clinics, composed by the prenatal clinic located inside the maternity hospital and the associated prenatal clinics located in the primary health centers of the area. Deliveries are assisted at the hospitals in both countries. Thus, the outcome will be assessed at the hospitals.

For cluster randomized trials with repeated cross-sectional binary measurements and a limited number of clusters, it is important to attempt to achieve as much balance as possible between the two arms of the study [31]. Based on the results of the initial assessment of health facility characteristics in the start-up phase of the study and using the baseline data, a “balanced randomization” technique [32] will be used to better achieve balance between the treatment groups in terms of the following characteristics of the prenatal clinics: frequency of women receiving the “5 A’s,” frequency of women who smoke during pregnancy, number of health providers/annual number of deliveries, proportion of midwives or nurse midwives who attend prenatal care/total of providers, and country. We have used similar randomization procedures in our recently published trial of a behavioral intervention to improve obstetrical care [28].

The analysis of the baseline data and the balanced randomization procedure will be performed by the study statistician, who will not be involved in the project management. Thus, there will be a clear separation between the generator of the intervention assignment and the study coordination [32].

### The intervention

#### Overview

Prenatal clinics allocated to the intervention group will receive an intervention divided in three phases and that will include the following activities; 1) Awareness phase: a) seminar to health providers and distribution of printed materials to increase awareness of the existence of the recommendations and program, b) identification of midwives interested in participating as facilitators of the program; 2) Training and persuasion phase: workshop for training on the “5 A’s” and for planning the implementation strategy; 3) Implementation phase: implementation of the program at the prenatal clinics identifying and training additional midwives to deliver the “5 A’s” and using reminders for health providers and patients. The intervention will be based on Roger’s “Diffusion of Innovations” theory [33] and will be tailored by formative research.

#### Theoretical basis

Roger’s “Diffusion of Innovations” theory [34] has been previously used in trials to implement programs at prenatal clinics, community schools, and home care associations [26]. Diffusion is defined as the process through which an innovation is communicated through channels over time among members of a social system [34]. An innovation is any idea, practice, service, or object that is considered new by an individual or social group, such as the “5 A’s” program. According to diffusion theory, certain characteristics of innovations increase the chances that they will be widely adopted. For example, the “5 A’s” program (innovation) would be more likely to be implemented and succeed if it is perceived as compatible with existing value systems and lifestyles. Roger’s theory describes five phases in the diffusion process: knowledge/awareness, persuasion, decision, implementation, and confirmation. The implementation of prenatal smoking cessation programs in prenatal clinics may follow a similar sequence with three phases: increase awareness about the importance and the availability of the programs; motivate, persuade, and train health providers; and planning and implementing the program.

We also based the intervention on two previously evaluated behavioral interventions based on Roger’s “Diffusion of Innovations” theory:

• The multifaceted intervention to promote the use of evidence-based childbirth practice evaluated by our group in Argentina and Uruguay, the Guidelines Trial [28]

• A behaviorally-based intervention designed to increase the number of hospitals that routinely provide effective smoking cessation programs in Queensland, Australia [26]

### Formative research

With the aim of ensuring that the intervention is effective, culturally-appropriate, and voluntarily integrated among women and health care providers into routine pregnancy care, formative research using qualitative and quantitative methods was carried out during the preparatory phase of the trial.

#### Qualitative component: focus groups and in-depth interviews

Focus groups and semi-structured interviews were conducted with prenatal care providers, hospital authorities and patients from selected public health care centers, which provide reproductive health and prenatal care in Buenos Aires, Argentina and Montevideo, Uruguay. The specific aims of this component were to identify the barriers and facilitators for the implementation of the “5 A’s” intervention at prenatal clinics, to assess pregnant smokers’ perspectives on adequate and readily accessible circumstances for the reception of the “5 A’s” strategy during routine prenatal care, and to assess pregnant women’s acceptability and opinions regarding specific self-help materials to increase sustainable smoking cessation during and after pregnancy.

#### Quantitative component: pilot study and preparatory survey

##### Pilot study

We will administer a questionnaire to women in the postpartum period admitted to six pre-selected maternity hospitals in Argentina (4 hospitals) and Uruguay (2 hospitals) where the outcomes will be measured. The objectives of the pilot study are to 1) pilot the questions to assess the main and secondary outcomes of the trial, 2) estimate the proportion of women who smoke and have received the “5 As” strategy during their prenatal care visits, among the women who deliver at the hospital, 3) assess agreement between saliva cotinine testing and self-reported smoking status, and 4) evaluate the proportion of women during postpartum hospital stay that consent to the questionnaire and saliva cotinine testing.

We will implement 200 interviews at each hospital during a one-month time frame (assuming refusals of slightly over 10%). Interviews will continue until we reach a total of 200 subjects at each hospital.

Trained interviewers, independent of the participating prenatal clinics, will be responsible for the administration of the questionnaire. Two shifts of interviews (one in the morning and one in the evening) will be organized to allow for interviewing women within the first 48 hours after delivery. The interviewers will identify all consecutive women that have undergone childbirth in the past 12 hours and that have received prenatal care at any of the participating prenatal clinics. After obtaining informed consent, they will proceed with the interview. This postpartum strategy for data collection has been proven feasible and successful in previous studies done by our group [35,36].

Each hospital must identify interviewers. Since the interview is relatively brief, some sites may prefer to have the health workers (e.g., nurses, nurse assistants) administer the survey interview. We will train the interviewers to screen, recruit, and interview the study participants.

Women will be informed about the study, invited to participate and asked to sign an informed consent. Women who agree to participate may refuse to answer any question and can withdraw from the study at any time. The informed consent will be read to the participant, her responses will be recorded, and a signed copy of the consent will be provided to the participant. Women may agree to answer the questionnaire and/or provide a saliva sample for cotinine test.

##### Preparatory survey

We will conduct this survey in all of the hospitals that will participate in the trial. The objectives of the study are: a) to estimate the number of women in a single month attending prenatal care at participating prenatal clinics who had their deliveries at the maternity hospitals; and b) to evaluate the process involved in a typical prenatal visit (e.g., average waiting time, personnel involved).

### Preparatory activities

To prepare the delivery of the intervention, the following activities will be conducted:

1. Tailoring the implementation intervention:

The results of the formative research will be used to refine the components of the intervention. Main points that will be confirmed or redefined will be: workshop format and length; recommended strategies to implement the smoking cessation program at the prenatal clinics; type and location of reminders; and educational materials to train health providers in the “5 A’s” for pregnant women and pregnancy-specific self-help materials to be provided to women within the “5 A’s” intervention.

2. *Adapting educational materials:*

a. Educational materials to train health providers in the 5 A’s.

The educational materials used in the workshops to train health providers conducted by the National Program of Tobacco Control in both countries do not include specific instructions on how to provide the “5 A’s” to pregnant women. We adapted pregnancy-specific materials from U.S. Agency for Healthcare Research and Quality (AHRQ) “Treating Tobacco Use and Dependence: Clinician's Packet. A How-To Guide For Implementing the Public Health Service Clinical Practice Guideline” [37] and from the UK National Institute for Health and Clinical Excellence’s guidelines for smoking cessation in pregnancy [38].

a. Pregnancy-specific self-help materials to be provided to women within the “5 A’s” intervention.

Currently, pregnancy-specific self-help materials are not provided to pregnant women by existing cessation programs. We will adapt materials for them from the same sources mentioned above for health providers.

3. Preparing seminars and workshops:

Contents of seminars and workshops will be defined, agendas will be detailed, and presentations and educational materials will be prepared and printed. The seminar and workshop will be piloted in Buenos Aires with a group of health providers working at similar but not participating prenatal clinics or maternity hospitals.

### Description of the intervention

The intervention will be tailored by formative research; therefore, the components described below could be modified after that stage.

#### Awareness phase

a) Seminar to health providers and distribution of printed materials

A seminar to all health professionals (physicians, nurses, and midwives) will be organized at the prenatal clinic in the hospital. The objectives of this component will be to present prenatal care providers with the problem of smoking during pregnancy, national recommendations for smoking cessation during pregnancy, the “5 A’s” intervention, the relevance of implementing the “5 A’s” intervention at the prenatal clinics, discuss activities planned with the implementation intervention.

b) Identification of facilitators

We intend to identify motivated midwives working at the prenatal clinics to serve as the facilitators who will be trained in the cessation program and then implement the program at their respective clinics. There are a number of reasons to select midwives over other types of health providers. In Argentina and Uruguay, midwives are trained to be primary prenatal caregivers and birth attendants. Midwives work as prenatal care providers at prenatal clinics in health centers. At hospitals, they mainly assist obstetricians. Thus, they have the opportunity and the necessary background to rapidly be trained in a smoking cessation program targeted to pregnant women. Women also respect the care and advice from midwives. Midwives have been proven as effective trained providers of the “5 A’s” in randomized-controlled trials [15]. Although physicians are prenatal care providers at hospitals, they usually dedicate a very short amount time to prenatal visits. In a study conducted in Mexico, Venezuela, and Panama in antenatal clinics, women spent a mean of 8–10 minutes in their physician’s office [39]. In another study performed in a public hospital in Buenos Aires among women receiving prenatal care, time spent with the provider was 14 minutes [40]. However, time spent at the clinic was longer (71–190 minutes in the four sites described); giving ample time for midwives to approach women for the implementation of the “5 A’s” intervention.

Nevertheless, if the formative research results in the consensus that general nurses and/or physicians can be included as facilitators, we will adapt this protocol to that purpose.

Facilitators will be identified by two ways after the initial seminar: 1) self nomination: those midwives that have an interest and are able to participate, and do not currently smoke, will be selected; 2) those midwives nominated by the health facilities’ authorities, and who are interested, will be selected. No initial limit in the number of facilitators will be considered. Considering the number of midwives available at the health facilities, we estimate that approximately 8–10 midwives will be selected per clinic.

#### Training and persuasion phase

Workshop for training on the “5 A’s” and for planning the implementation strategy.

The facilitators will participate in a 1.5 day workshop conducted in either Buenos Aires or Montevideo. Prenatal clinics’ health authorities will be invited to participate or to designate a delegate. The workshops will be given in previously selected sites outside of the prenatal clinics and will be conducted by a specialized trainer in smoking cessation programs. Interactive workshops have been proven an effective strategy for guidelines implementation [41].

The objectives of the workshop will be: to train facilitators on the “5 A’s” intervention (training of the trainers); to train facilitators on the suggested strategies to implement the “5 A’s” intervention program at their prenatal clinics; and to develop a dissemination and implementation plan.

The workshop will be adapted from the current workshops delivered by the National Tobacco Control Programs in Argentina and Uruguay [42]. Suggested topics to be included are: general overview of smoking prevalence and trend in Argentina/Uruguay; health consequences of smoking during pregnancy, specifically for the mother and the newborn baby; roles of the health care provider in preventing smoking among pregnant women; current recommendations and expected situation; brief explanation of smoking as an addiction; levels of interventions to promote smoking cessation; brief intervention “5 A’s”; assessing who is ready to quit and who is not; motivational interviews; role play; medications for smoking cessation; implementing the “5 A’s” in the prenatal clinic. We will also ask participants to create a plan to implement the “5 A’s.”

#### Implementation phase

During the implementation phase, each team of facilitators and prenatal clinic authorities will be responsible for organizing the “5 A’s” smoking cessation program in their prenatal clinics. The aim will be to ask all prenatal patients their smoking status and to then offer counseling and support included in the “5 A’s” intervention to all pregnant women who describe themselves as smokers. To this purpose, we will suggest to facilitators the following strategies to be considered in the implementation plan. First, they should identify the health providers who will deliver the “5 A’s” to pregnant women. Second, they will train the selected providers if they have not already received the training as facilitators. Finally, they will encourage use of reminders to be displayed in the prenatal clinic waiting rooms, clinical records, and the prenatal care.

### Activities in the control group

The control group will receive no intervention after randomization but will be asked to continue with standard in-service training activities. The control group will receive the intervention components after the intervention phase is completed.

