## Methods

### Overview

We will conduct a two-arm, parallel cluster randomized-controlled trial with baseline and follow-up cross sectional measurements in 20 prenatal care settings in Argentina and Uruguay. Prenatal care settings will be randomly allocated to either an intervention or a control group after a baseline data collection period. The intervention will include identification and training of midwife facilitators on the “5 A’s.” The facilitators will then disseminate and implement the smoking cessation program at their prenatal care settings. The prenatal care settings in the control group will continue with their standard in-service activities. A follow-up data collection period will be conducted in all hospitals. The intervention will be tailored by formative research to be readily applicable to local prenatal care services at busy maternity hospitals and to be acceptable to local pregnant women and health providers (Figure 1).

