#### Data collection and management

Outcome data will be collected in two six-month periods at all participating prenatal clusters: a baseline period and a follow-up period, separated by the intervention phase during which no outcome data will be collected. During the six-month data collection periods we will collect data on ≥200 women who have received prenatal care at each of the participating clinics. Outcome data will be collected in the maternity hospitals where women attending prenatal care at the participating prenatal clinics deliver. Process data will be collected during the intervention phase and only at intervention prenatal clinics.

Trained interviewers, independent of the participating prenatal clinics, will be responsible for the administration of the questionnaire to women, including obtaining the saliva samples. To allow for interviewing women within the first 12 hours after deliveries, two shifts of interviews will be organized: one in the morning and another in the evenings. The interviewers will identify all consecutive women who have undergone childbirth in the past 12 hours and who have received prenatal care at any of the participating prenatal clinics. After obtaining informed consent, they will interview each woman and obtain the saliva sample (if the woman is eligible). Demographic and childbirth data will be extracted from the clinical record. Cotinine samples will be kept refrigerated and then frozen in order to keep them in the appropriate conditions until shipment to CDC for analysis. This postpartum strategy for data collection has been proven feasible and successful in previous studies of our group [35,36].

Data will be collected on paper forms designed specifically for the study. A digital image of the interview form will be taken and sent to the local data center for data entry, but the inclusion form and the hard copy of the interview form will remain at the hospital until the end of the data collection period. With this system, it is ensured that personal identifiers will not be taken from the hospital and will be kept securely by the hospital staff.

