### Sample size

The sample size is based on both primary and secondary objectives. A pre-test post-test (2 time–points) nested cross-sectional design was planned with 10 intervention and 10 control clinics. Each intervention and control group will contain seven clinics, with a minimum of 200 women at each time point, and three smaller clinics, with a minimum of 120 women at each time point. For each objective, the statistical power was estimated using a Monte Carlo simulation with 3,000 repetitions. In the simulation, binary outcomes from women were generated from the proposed pre-test post-test nested cross-sectional design under the following assumptions:

• An increase in the frequency of women receiving the “5 A’s” at the end of pregnancy from 10% to 20% in the control group and from 10% to 50% in the intervention group (i.e., an intervention effect of 30%) for the primary objective.

• A decrease in the frequency of women who smoke at the end of the pregnancy from 18% to 17% in the control group and from 18% to 12% in the intervention group (i.e., an intervention effect of 5%) for the secondary objective.

• An intra-cluster correlation between 2 outcomes from different women at different times (pre-test/post-test) = Intra-cluster correlation between 2 different women at the same time of 0.05. The value of the latter intra-cluster correlation coefficient was observed in a study carried out in Argentina and Uruguay [3].

For this sample size, the estimated statistical power at the 5% level of significance (2-sided) is 1.0 for the primary objective and 0.89 for the secondary objective.

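### Control clinics' access to the intervention is tied to the end of the intervention phase, not the end of follow-up, so the wording allows control training while outcomes are being measured

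*Protocol article*

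**What the plan says.** Two sentences under Activities in the control group set the control condition. The first is "The control group will receive no intervention after randomization but will be asked to continue with standard in-service training activities". The second is "The control group will receive the intervention components after the intervention phase is completed".

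Data collection and management fixes the calendar. "Outcome data will be collected in two six-month periods at all participating prenatal clusters", and these are "a baseline period and a follow-up period, separated by the intervention phase during which no outcome data will be collected". The Overview of the Methods adds: "A follow-up data collection period will be conducted in all hospitals".

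The order is therefore baseline, intervention phase, follow-up, with both arms measured in the last period. No section of the article says that delivery to control clinics waits for follow-up to close, and none says that it begins at once.

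**The concern.** The milestone that releases the intervention to control clinics is the same one that opens follow-up measurement. A site team could train control clinics during those six months without deviating from the protocol.

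The outcome is open to this. Women are asked after delivery what counselling they received during prenatal care, and the article gives a mean of 7 visits. A woman delivering late in follow-up could have had several visits after her control clinic was trained. Under intention to treat she still counts as a control.

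The damage would be hard to detect. Process data are collected only in intervention clinics and only during the intervention phase, so early uptake in controls would not be recorded there. A rise in the control rate would also be hard to tell apart from the background rise, 10% to 20%, that the sample size already assumes. Both contrasts would shrink toward zero, and the loss could not be recovered afterwards.

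**Working it through.** **Inputs, all from Sample size and Statistical analysis.**
- Design: "nested cross-sectional design was planned with 10 intervention and 10 control clinics". In either arm, seven of the ten clusters contribute at least 200 women per period and the other three at least 120. Women per arm and time point: 7 × 200 + 3 × 120 = 1,760.
- Receiving the 5 A's: control 10% to 20%, intervention 10% to 50%.
- Smoking at the end of pregnancy: control 18% to 17%, intervention 18% to 12%.
- Intra-cluster correlation 0.05, the same within and across periods.
- Tests: t-test on cluster changes for the primary outcome; GEE arm-by-time interaction for smoking.

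**Step 1: reproduce the plan's figure.** The plan states that "the estimated statistical power at the 5% level of significance (2-sided) is 1.0 for the primary objective and 0.89 for the secondary objective". A simulation with 3,000 repetitions and a cluster effect shared across the two periods gives 1.00 for the primary outcome. For smoking it gives 0.894 to 0.896 with beta or logit-normal cluster effects. An additive cluster effect gives 0.83 for smoking, and a cluster-level t-test gives 0.72 to 0.76. The stated power is thus reproduced by the GEE analysis the plan names. It assumes control follow-up rates of 20% and 17%, that is, untreated controls.

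**Step 2: dilute.** Let f be the share of the intervention effect that reaches control women measured at follow-up. The documents do not give f, so it is varied.
- Primary: control rate = 20 + 30f, so difference = 50 − (20 + 30f) = 30(1 − f) points.
- Smoking: control rate = 17 − 5f, so difference = (17 − 5f) − 12 = 5(1 − f) points.

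**Step 3: power at each f** (beta cluster effects, two-sided 5%).

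| f | Control 5 A's | Primary difference | Primary power | Control smoking | Smoking difference | Smoking power |
|---|---|---|---|---|---|---|
| 0 | 20% | 30 | 1.00 | 17% | 5 | 0.90 (plan: 0.89) |
| 0.10 | 23% | 27 | 1.00 | 16.5% | 4.5 | 0.84 |
| 0.25 | 27.5% | 22.5 | 1.00 | 15.75% | 3.75 | 0.70 |
| 0.50 | 35% | 15 | 0.995 | 14.5% | 2.5 | 0.44 |
| 0.75 | 42.5% | 7.5 | 0.66 | 13.25% | 1.25 | 0.18 |

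At f = 1 both differences are zero. With no true difference the simulated GEE test for smoking still rejects in about 0.09 of runs, so the lower smoking figures are, if anything, generous.

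The primary test has a wide reserve, although its estimated effect is halved at f = 0.50. The smoking objective has little: power drops below 0.80 somewhere between f = 0.10 and f = 0.25.

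**The case against.** The strongest reply is that *after* sets an earliest point, not a start date. Delivery once follow-up has closed also satisfies the sentence. The sentence before it denies controls any intervention after randomization, and the sample size assumes untreated control rates at follow-up. Read together, these suggest an ordinary promise of delayed access with the phase named loosely. The trial design figure, which may settle the order, is not visible in the text available, and the article condenses a fuller protocol.

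Much of this stands. A reader might infer that control clinics will be trained the day follow-up opens, and that the control arm is therefore contaminated. The documents do not say so. Even with immediate release, exposure would build slowly: the intervention runs through a seminar, choice of facilitators, a workshop and onward training, and women delivering early in follow-up would have had most of their care beforehand.

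A reader might also infer that power for the primary outcome collapses. On the plan's own inputs it is 0.995 at 50% dilution. A steep fall at that level needs a smaller denominator, such as smokers only, or a larger intra-cluster correlation; the plan's power calculation uses neither.

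What the reply does not remove is that the written milestone is the wrong one. The denial of intervention after randomization is qualified by the very next sentence, which ends it at completion of the intervention phase.

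**Conclusion.** The point holds as a defect of wording with a real consequence if sites act on it early. The rule permits exposure of control clinics during outcome measurement; it neither requires it nor shows that it is intended. Bias would run toward no effect, so it could not by itself create a false positive.

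The size depends entirely on the assumed f. From f = 0.25 to f = 0.50 the primary effect falls from the planned 30 points to between 22.5 and 15, with power still at least 0.995. Over the same range smoking power falls to between about 0.70 and 0.44. These figures rest on the plan's cluster sizes, rates and correlation, and on both outcomes being diluted by the same share. The smoking objective is the one exposed to a missed effect; for the primary outcome the risk is mainly an underestimate.

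**What to change.** Replace the second sentence under Activities in the control group with wording such as: *Control clinics will receive the intervention components only once the six-month follow-up data collection has closed in all clusters.* Check that Data collection and management and the trial design figure show the same order, and settle this before follow-up opens.

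The planned effects and the stated power of 1.0 and 0.89 then keep the untreated-control basis on which they were calculated. The change is one sentence, with no change to sample size or analysis. Its cost falls on the control clinics, which wait about six months longer than the earliest date the present wording allows.
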